## Abstract

We develop a protocol for assessing the impact of an intervention aimed at improving sleep quality among university nursing students. The study is designed as a pilot randomized controlled trial to be applied during the 2022-23 academic year and is registered at Clinical Trials Gov website (NCT05273086). A total of 60 nursing students will be recruited from a Spanish university. They will be divided into two groups: (30) intervention group and (30) control group. The intervention group will attend two cognitive–behavioural therapy sleep programme sessions focused on knowledge of anatomical structures involved in sleep, chronotype, synchronization, and good sleeping habits. Subjective and objective sleep quality will be assessed before and after the intervention for both groups. In addition to sleep quality, socio-demographic parameters, physical activity, lifestyle habits, and anthropometric measures will be considered prior to intervention. Finally, a satisfaction questionnaire will be applied for posterior analysis. This study is an innovative, relevant intervention that aims to improve sleep quality among university nursing students. Both the approach and the use of objective and subjective validated outcome measurements are key features of this study.

## 1. Introduction

Sleep has been defined as an essential brain state for maintaining energy and restoring bodily function [1]. Sleep quality has a huge impact on health [2], and it is considered a leading public health problem [3]. Although there has been interest in sleep quality in different disciplines such as nursing, medicine, and psychology, it has not yet been clearly defined from a neurophysiological point of view. The concept analysis by Nelson et al. [4] shows that sleep quality is determined by five components: (1) sleep efficiency, total sleep time-total time in bed ratio; (2) sleep disturbance; (3) sleep latency, defined as the time taken to pass from wakefulness to sleep; (4) sleep duration in 24 h; (5) and waking after sleep onset, or in other words, the total time awake from sleep onset to finally waking up.

Good sleep quality is a predictor of physical and mental health, well-being, and overall vitality [5]. However, poor sleep quality, determined by a negative subjective perception of sleep, sleep onset times, short sleep duration, and difficulties combining sleep and daytime activity [6], has been related to psychiatric disorders such as depression, anxiety, and cognitive difficulties, with reduced physical health, premature ageing, and lower efficiency at work [7].

University students are one of the population groups that suffer most sleep-related problems. Both lack of sleep and sleep disorders are the main characteristics involved in low sleep quality among university students [8]. Over time, it has been noted that the weekly sleep pattern of this group is determined by few hours sleeping during the week and recovering sleeping hours at the weekend [7,9]. This deregulation causes them to experience delayed sleep phase syndrome [10], which is characterised by difficulty falling asleep at a socially acceptable time of night and inability to wake easily in the morning [11]. This syndrome has been related to poor academic performance, behavioural, emotional, and psychological problems, as well as increased drug and alcohol consumption [12]. 

Nursing students face complex situations that can specifically affect their sleep quality [13]. Different factors have been identified as limiting the quality of sleep of this group, especially during the first year of professional training [14]. There were individual psychosocial factors [15,16,17], regarding the academic area and professional environment where they describe the possibility of making mistakes in care practice and handling equipment, as well as lack of knowledge and professional skills [18]. 

Several studies have implemented intervention programmes to improve sleep quality among the adult population without resorting to the use of drugs [19]. However, the published literature among the university student population with no prior sleep-related pathologies is scarce, despite the fact that they are considered a high-risk group. To the best of our knowledge, only one systematic review [20] and a meta-analysis [21] that address interventions to improve sleep in university students have been published so far. The latter includes 14 studies, of which six were conducted with university students and the rest with young students and adolescents. 

Many interventions in both the general population and university and adolescent populations focus on treating insomnia and mental health problems such as anxiety and depression. These works have a practical approach to sleep quality, but they do not take into account fundamental elements such as circadian rhythms, motor activity, skin temperature, sleep phases and position in 24 hours, which are key to understanding sleep quality and being able to improve it [22,23,24].

Interventions to improve sleep quality generally have several fundamental cornerstones. First, students are unaware of how sleep deprivation or disturbance affects cognitive functioning [10]. This justifies educational interventions to understand how the brain regulates sleep function. Despite some studies suggesting that people suffering insomnia who receive theoretical sleep training can significantly improve sleep quality [25], the relationship between knowledge and better sleep quality is unclear [10]. Thus, interventions should have a multi-factor approach including different elements that provide attendees with tools to improve their sleep. 

Several studies indicate that cognitive-behavioural therapy yields positive results in this type of intervention [26] as it involves improving sleep by modifying mindset and behaviour patterns. Therapy has different types of treatment that can be used individually or in combination, such as relaxation, stimulus control, restricting sleep and sleep hygiene [27]. Cognitive–behavioural therapy has a multi-component nature, so it can be used to improve health in relation to sleep quality when there is no associated pathology [20]. This is the case of specific sleep hygiene and stimulus control techniques related to sleep [26] which focus on health. Sleep hygiene appears to be a key factor in these interventions as it addresses a series of behavioural and environmental recommendations aimed at promoting healthy sleep from a psychoeducational perspective. During education on sleep hygiene, users learn about healthy sleep habits, which is a first-line intervention for promoting sleep health [26,28].

Assessing interventions to improve sleep quality is another issue that needs to be addressed. The complex nature of the construct requires the use of objective (external and metric assessment) and subjective (perception of sleep quality) aspects in its assessment. Polysomnography and actigraphy are two different methods used to measure sleep quality [4]. For a subjective sleep assessment, the *Pittsburgh Sleep Quality Index, PSQI* [20] is typically used. Polysomnography is the gold standard method [29], but its use is limited due to difficult availability and home monitoring, combined with the lack of other validated outpatient tools that can replace this test [30]. Studies often use actigraphy to assess sleep [21] because it has proven to be sensitive in its measurement, but again it is of limited use for certain parameters, such as wakefulness during the night. This means that it is not a complete measure for assessing sleep quality and cannot be considered validated like polysomnography [24]. There are no studies using both measures as complementary measures to obtain data on sleep quality in adults [19], and more specifically in young people and adolescents [26]. In fact, most of the systematic review studies mentioned above use PSQI or actigraphy, translating the results into total hours of sleep [20,21]. This leads to a partial and biased assessment of how these interventions affect sleep quality.

Lastly, despite numerous studies analysing the factors associated with poor sleep quality in nursing students [7,31], no intervention study was found in the literature to design, implement, and assess an interventional programme to improve sleep quality in this group.

The aim of this study is to develop a protocol for assessing the impact of an intervention aimed at improving sleep quality among nursing university students.

## 2. Materials and Methods

The study protocol is based on a randomized controlled trial. Participants will be randomly assigned to a control and an intervention group. Only participants in the latter group will receive the intervention based on two cognitive–behavioural therapy sleep programme sessions.

### 2.1. Hypotheses

We pose the conceptual hypothesis that participants in the intervention group will improve their sleep quality, measured by objective monitoring parameters, and their subjective perception. 

### 2.2. Design

The study will be conducted at a Spanish university as a two-arm pilot randomized clinical trial (intervention and control). It will be single-centre and single-blind (data analysts), comparing two conditions: the intervention group (IG), with a specific intervention on sleep quality, and the control group (CG), with no intervention. Figure 1 shows the study flow chart. The random clinical trial report will follow the recommendations for interventional trials (SPIRIT) [32]. This protocol is registered at ClinicalTrials.gov (accessed on 15 September 2022) with reference number NCT05273086. 

### 2.3. Sample/Participants

The study will be conducted at a university in Madrid (Spain). The intervention environment will be exclusively affecting undergraduate students during the first term of the 2022-23 academic year (October 2022–February 2023).

#### 2.3.1. Inclusion Criteria

Students aged 18 to 25 years.Students enrolled in their first full year of a nursing degree, 2022-23.

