#### 2.3.2. Exclusion Criteria

Prior mental pathology and/or sleep disorder diagnosis with or without medication (hypnotics, sedatives, and melatonin).Participants that use any drugs to sleep.Combining work and studying.

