#### 2.5.1. Dependent Variables

Sleep quality: Kronowise 3.0, Kronohealth, S.L., Spain. Kronowise 3.0 is a wrist device that conducts ambulatory circadian monitoring (ACM) based on thermometry, motor activity, and body position (TAP). TAP uses a combination of sensors in an algorithm that has been validated as ambulatory polysomnography. It was validated by comparing the assessment of these parameters with polysomnography in adults [35] and in patients diagnosed with Parkinson’s [36]. The device can measure sleep quality and circadian rhythms and identify circadian chronodisruption through parameters such as sleep latency, total sleep time (in minutes), sleep efficiency, number of awakenings and time between waking and sleep [35]. It can also identify sleep phases, nocturnal awakenings, temperature, exposure to infrared and blue light as well as other parameters such as time in bed, sleep onset, awake time, sleep interval, total time in movement, time in movement index, sleep acceleration index, wrist sleep temperature, napping time and napping frequency [36]. Participants will wear the device for seven consecutive days, including weekdays and weekends. Both groups will be measured twice (before and after the intervention), meaning that all participants will wear the device for a total of 14 days. Participants will be given appointments to fit and remove the devices. Information provided by the devices will be entered into the software that will be sent to Kronohealth S.L., Spain, which will produce reports of both measurements with the results of the parameters mentioned above, with the sleep quality indices established according to the device validation [35].Perceived sleep quality: Pittsburgh Sleep Quality Index, PSQI [37]. The PSQI contains 19 items and seven clinically important components related to sleep quality: subjective sleep quality, sleep latency, sleep duration, sleep efficiency, sleep disturbances, use of sleeping medication, and daytime dysfunction. Responses will be reported based on a Likert-type scale from 0 to 4. Overall sleep scores of 5 or less will be considered good quality, whereas scores of 5 or more will be considered low quality. The PSQI version that will be used is validated into the Spanish university framework by De la Vega et al. [37] with a Cronbach’s alpha of 0.72. The questionnaire will be given to all participants twice (before and immediately following the intervention).

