### 2.8. Data Analysis

For the statistical analysis, all variables will be coded by using IBM Statistics SPSS v.21 software (Chicago, USA) for Windows and revised twice. A protocol approach will be followed where missing data will not be included in the analysis.

All descriptive statistical parameters will be expressed as absolute (‘n’) and relative (‘%’) frequencies for each qualitative variable category. Quantitative variables will be analysed with the mean, median, and standard deviation to observe their behaviour at a confidence interval of 95%. Normal variable distribution will be analysed by using the Kolmogorov–Smirnov test with Shapiro–Wilk correction. 

A repeated measures ANOVA will be used to compare mean differences between the intervention and control groups over time, considering the time–group interaction effect. The size of the effect will be analysed based on Cohen’s d [40]: 0–0.3 low, >0.3–0.8 moderate, and >0.8 large effect size. Any incomplete questionnaires will be excluded from the analysis. Results will be considered statistically significant when *p* < 0.05.

The PROCESS macro will be used to examine the mediating effects of sleep quality on the relationship between attending the sleep intervention or not. This analysis uses linear regression to estimate indirect effects according to Hayes and Rockwood’s methods recommended for clinical studies and focuses on two measurement moments [41]. Post-treatment scores will be added as mediators, and baseline scores for the outcome variables and mediators will be added to the models as covariates. Least-square path analysis will be used and the bootstrap confidence interval (5000 permutations) will be applied to estimate indirect effects.

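### Baseline PSQI is collected but used neither in allocation nor in the main comparison, although good sleepers may enter, so a null average effect would say little about poor sleepers

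*Protocol article*

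**What the plan says.** - **Entry (Sections 2.3.1 and 2.3.2).** The inclusion criteria are "Students aged 18 to 25 years.Students enrolled in their first full year of a nursing degree, 2022-23". The exclusions include "Prior mental pathology and/or sleep disorder diagnosis with or without medication (hypnotics, sedatives, and melatonin") and "Participants that use any drugs to sleep". No baseline sleep score is required.
- **Aim (Section 2.1).** The hypothesis is that "participants in the intervention group will improve their sleep quality, measured by objective monitoring parameters, and their subjective perception".
- **PSQI (Section 2.5.1).** The classification reads "Overall sleep scores of 5 or less will be considered good quality, whereas scores of 5 or more will be considered low quality". On timing: "The questionnaire will be given to all participants twice (before and immediately following the intervention").
- **Allocation (Sections 2.3.4 and 2.7).** Permuted blocks at 1:1 are used, and no stratification factor is named. Students are randomised when recruitment closes. The pre-intervention assessment is listed among the phases that follow. Section 2.3.5 states that participants are not blinded.
- **Analysis (Section 2.8).** "A repeated measures ANOVA will be used to compare mean differences between the intervention and control groups over time, considering the time–group interaction effect". Baseline scores appear as covariates only in the mediation models.
- **Rationale (Sections 1 and 3).** Students without sleep pathology are presented as an under-studied, high-risk group, and the programme as promotion of healthy sleep. The limitations name sample size, contamination and device availability. They do not mention the baseline mix of good and poor sleepers.

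**The concern.** A low PSQI score means good sleep. A student who starts at 2 or 3 can fall only a few points, and the sleeping-medication component starts close to zero because users of sleep drugs are excluded. If such students enter and respond less, the average effect on the PSQI is smaller than the effect in those with room to improve. A null average could then mean that the programme does not work, or that it works in poor sleepers and the average hides this.

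The baseline PSQI could reduce this problem, but the plan gets little from it. The score does not balance the arms. With two time points, the time-group interaction is the comparison of mean change scores, which is less precise than adjustment for baseline. Because the questionnaire follows allocation, an unblinded participant may also answer the baseline knowing his or her group.

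**Working it through.** **Inputs from the article.** 30 per arm (Abstract); an expected medium effect, a target of 60 and a population of 70 (Section 2.3.3); p < 0.05 (Section 2.8); ten devices, one week per student (Section 2.7).

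**Assumptions of this check.** Medium means d = 0.5, in units of the SD of the compared score; the test is two-sided; p is the share of good sleepers; k is their effect relative to poor sleepers; r is the pre-post correlation of the PSQI. The article gives none of p, k or r.

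**1. The plan's own figure.** The survey-precision part of Section 2.3.3 reproduces: n0 = 1.96² × 0.25 / 0.05² = 384.2, and with finite-population correction 384.2 / (1 + 383.2/70) = 59.3, rounded up to 60. As a two-group size, 60 does not follow from d = 0.5. The usual formula gives 126 in total for 80% power.

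**2. Power before any dilution.** t test with 58 degrees of freedom and noncentrality 0.5 × √(30/2) = 1.94: power 48% (49% by normal approximation).

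**3. What dilution could do.** d_mix = 0.5 × [(1 − p) + k × p], with the same t test:

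| p (good sleepers) | k | d_mix | Power |
|---|---|---|---|
| 0 | – | 0.50 | 48% |
| 0.2 | 0 | 0.40 | 33% |
| 0.4 | 0 | 0.30 | 21% |
| 0.6 | 0 | 0.20 | 12% |
| 0.2 | 0.5 | 0.45 | 40% |
| 0.6 | 0.5 | 0.35 | 27% |

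These rows only show how strongly the result depends on p and k. They do not estimate this trial's dilution. The first row shows that power is low even with no good sleepers.

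**4. What the baseline score could buy.** With equal SDs before and after, the variance of the group difference is proportional to 2(1 − r) for change scores and to 1 − r² for baseline adjustment. The ratio is (1 + r)/2.
- r = 0.3: 0.91 / 1.40 = 0.65, a 35% reduction.
- r = 0.5: 0.75 / 1.00 = 0.75, a 25% reduction.
- r = 0.7: 0.51 / 0.60 = 0.85, a 15% reduction.

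**5. Balance.** With 24, 30 or 36 poor sleepers among 60 (assumed) and 30 drawn at random, the hypergeometric probability that the arms differ by 6 or more poor sleepers is 18.7%, 19.6% and 18.7%. Small blocks without strata do not change this materially.

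**6. What an interaction could show.** Assume half are poor sleepers (15 per cell), SD 1 and 56 degrees of freedom (t = 2.003). The 95% half-width for the effect in poor sleepers is 2.003 × √(2/15) = 0.73 SD. For the difference between the two effects it is 2.003 × √(4/15) = 1.03 SD. This is too wide to decide between the two explanations of a null.

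**The case against.** The strongest reply is that the population is intended. The introduction argues for studying students without sleep pathology, and the average effect in unselected first-year students is a legitimate target that the randomised comparison estimates. This stands, although the rationale covers the absence of pathology and does not discuss students who already sleep well. A sleep threshold at entry would also shrink a pool of only 70.

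Several stronger readings are tempting but unsupported:
- **That the criteria remove the worst sleepers.** They remove diagnosed or medicated students. Undiagnosed poor sleepers remain eligible.
- **That about half the sample has nothing to improve.** No baseline distribution is given, and a score of up to 5 is not zero room. Nothing shows that good sleepers on the PSQI lack room on the wrist-device measures.
- **That power drops from a comfortable level because of dilution.** Starting from d = 0.8, with 40–70% poor sleepers and 0–25% of the effect in good sleepers, power falls from 86% to 23–66%. The arithmetic is correct, but the article expects a medium effect, and 0.8 is the top of its own moderate band.
- **That a null would be uninterpretable.** It would still inform on the average effect, and baseline PSQI is collected for everyone.

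The chance imbalance is ordinary random variation already allowed for in the standard error. Stratifying improves balance and precision and does not repair a bias. Moderator analyses may properly be left to an analysis plan that is not shown. Entry, allocation and the main model, however, are fixed in this article.

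**Conclusion.** The point holds as a cheap improvement to the design and does not make the trial invalid. Good sleepers may enter with limited room to improve on the PSQI. The dilution is plausible but of unknown size, and a null average would be ambiguous about poor sleepers. Low power (about 48% at an assumed d = 0.5, before any dilution) and the contamination that the article acknowledges already make a null hard to read.

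The quantifiable gain is a 15% to 35% lower variance of the PSQI effect from baseline adjustment, for an assumed r of 0.7 down to 0.3 and equal SDs. Taking the PSQI before allocation also removes the chance that knowledge of the group colours the baseline answer. The article gives no evidence on how large that influence would be. None of these changes makes the average effect less diluted.

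**What to change.** Keep the entry criteria.
1. Make the PSQI cut-off unambiguous, because a score of 5 currently falls in both classes.
2. Collect the PSQI with the consent forms, before allocation, and run the permuted blocks separately within the two PSQI strata. All students are randomised together after recruitment closes, so this needs only a two-stratum list.
3. Analyse the post-intervention PSQI by group with baseline PSQI as a continuous covariate, in place of the unadjusted time-group ANOVA.
4. Report the group-by-baseline-PSQI term only as an exploratory estimate with its 95% CI.
5. State that a null result will be read as a statement about the average effect in unselected students, not as absence of benefit in poor sleepers.

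**Cost.** One existing questionnaire moves forward, the list has two strata and the model changes by one covariate. The interaction will be very imprecise at n = 60. Ten devices at one week each spread the baseline of 60 students over at least 60 / 10 = 6 weeks, so a PSQI taken at consent may precede the device baseline by weeks and may need repeating at the device visit. If it is repeated, the protocol should say which of the two scores is the covariate. The pre-allocation score is the one that knowledge of the group cannot affect.

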#### 2.3.2. Exclusion Criteria

Prior mental pathology and/or sleep disorder diagnosis with or without medication (hypnotics, sedatives, and melatonin).Participants that use any drugs to sleep.Combining work and studying.

#### 2.3.3. Sample Size Calculation

For a population size of 70, at least 60 samples are required to have a confidence level of 95% so that the real value is within ±5% of the measured/surveyed value. For two-group comparisons, at least 60 samples are required for an expected medium effect [33].

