#### 2.3.4. Randomization

An independent researcher who is unaware of the study characteristics will conduct the random assignment procedure. A computer-generated random number sequence (Sealed Envelope™ software version 1.21.0, London, UK), assigned to participants’ academic record number will be used to randomly designate participants to one of the two groups (IG or CG). Random permuted blocks will also be used to reduce the random sequence predictability and guarantee a 1:1 ratio. This sequence will be password-protected in a table and will be hidden from other researchers during the study.

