## 4. Conclusions

The methodological design of this study supports interventions that can favour better sleep quality in university nursing students. The intervention is a novel strategy combining cognitive learning about sleep as a physiological process, the use of technological devices to monitor sleep parameters, and addressing students’ knowledge about their individual habits through cognitive behavioural therapy. The research to be conducted using this protocol aims to demonstrate the positive effect of such an intervention on sleep quality in nursing students. 

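### Neither reason given for 60 students supports the two-group comparison: one is a survey-precision formula, and the medium-effect claim states no power and fails on its usual reading (48% power at d = 0.5)

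*Protocol article*

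**What the plan says.** Section 2.3.3 (Sample Size Calculation) has two sentences. The first takes a population of 70 and a margin of ±5% and concludes that "at least 60 samples are required to have a confidence level of 95"%. The second says: "For two-group comparisons, at least 60 samples are required for an expected medium effect", with a literature citation and nothing more. It gives no power, numerical effect, sidedness, test, pre-post correlation or dropout allowance.

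The Abstract sets the arms at 30 and 30, and section 2.3.4 uses permuted blocks to "guarantee a 1:1 ratio". Section 2.8 plans a repeated measures ANOVA with a time-by-group interaction and sets the threshold: "Results will be considered statistically significant when *p* < 0.05". It grades Cohen's d as "0–0.3 low, >0.3–0.8 moderate, and >0.8 large effect size".

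The Abstract and section 2.2 call the trial a pilot. The Discussion (section 3) concedes that the sample may be too small to show group differences. Section 4 says the research "aims to demonstrate the positive effect of such an intervention on sleep quality in nursing students".

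**The concern.** A sample-size section should tell the reader what the trial can detect or how precisely it will estimate. Here the first sentence answers a different question: how closely one percentage can be estimated by sampling most of a small population. Only the second addresses the comparison that will be analysed, and it lacks the inputs needed to check it.

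Since the trial enrols exactly 60, the second sentence works as a statement that the size is adequate for a medium effect. If it is not, a reader of a non-significant result has been given a wrong idea of what that result can rule out. A later, larger trial that copies this reasoning would inherit the problem.

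**Working it through.** **Inputs from the article:** 30 per group (Abstract); 1:1 allocation (2.3.4); significance level 0.05 (2.8); moderate d above 0.3 and up to 0.8 (2.8); population 70 and ±5% (2.3.3).

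**Assumptions, because the article gives no figure:** two-sided testing; d = 0.5 as the conventional medium effect, on the SD of the outcome at one time point; 80% as the conventional power target; pre-post correlation r from 0 to 0.8.

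**1. The plan's first figure.** For a proportion of 0.5, n0 = 1.96² × 0.25 / 0.05² = 384.16. With the finite-population correction, n = 70 × 384.16 / (384.16 + 69) = 59.3, so 60. The figure reproduces. The formula contains no second group, no difference and no power.

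**2. The plan's second figure, as a two-group comparison at one time point.** The noncentrality is d × √(30/2), with 58 degrees of freedom. At d = 0.5 it is 0.5 × 3.873 = 1.94. The noncentral t distribution gives:

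| d | Power, 30 per group |
|---|---|
| 0.3 | 21% |
| 0.5 | 48% |
| 0.6 | 63% |
| 0.7 | 76% |
| 0.74 | 80% |
| 0.8 | 86% |

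For 80% power at d = 0.5, 64 per group are needed, 128 in total (126 by the normal approximation). One-sided testing would still need 100. So 60 is not recovered at d = 0.5 and 80% power. Within the plan's own moderate band it fits only the top end, from about 0.74.

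**3. The planned test.** With two time points, the time-by-group interaction is a comparison of change scores. The SD of change is √(2(1 − r)) times the outcome SD, so d = 0.5 becomes 0.5 / √(2(1 − r)). The d detectable with 80% power is 0.736 × √(2(1 − r)). The 95% confidence interval half-width for the difference is t(58) × √(2/30) × √(2(1 − r)) = 0.517 × √(2(1 − r)) outcome SD.

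| r (assumed) | Power at d = 0.5 | d at 80% power | CI half-width (SD) |
|---|---|---|---|
| 0 | 27% | 1.04 | 0.73 |
| 0.5 | 48% | 0.74 | 0.52 |
| 0.7 | 69% | 0.57 | 0.40 |
| 0.8 | 85% | 0.47 | 0.33 |

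The planned test matches the simple comparison at r = 0.5 and passes 80% only near r = 0.8 (77% at r = 0.75).

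**4. A possible alternative meaning of medium.** If it meant f = 0.25 for the interaction, 60 students would give 77% power at r = 0 and 97% at r = 0.5. In a two-by-two layout, however, the difference in change is 4 × f = 1.0 outcome SD. Section 2.8 calls anything above 0.8 large.

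**The case against.** The strongest reply is that nothing has been shown to be false. The sentence states a minimum, not that 60 is enough. The effect of 0.5, two-sided testing and 80% power are all supplied by the reader. The cited source is not at hand, and an article may leave inputs to the full protocol. The moderate band extends to 0.8, where power is 86%, and a high correlation would rescue d = 0.5 as well. The trial is called a pilot, and the Discussion admits the limit.

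Much of this stands, and it rules out several stronger readings that a reader might infer:

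- **That the section contains a proven arithmetic error.** One figure reproduces and the other lacks the inputs that would let it be refuted outright.
- **That the trial simply has 48% power.** For the planned test this holds only at r = 0.5, and the article gives no correlation.
- **That no estimate from this trial can be within ±5%.** A baseline proportion in all 60 of the 70 has half-width 1.96 × √(0.25/60 × 10/69) = 0.048, or ±4.8 points. The sentence is irrelevant to the comparison, but it is not numerically wrong.
- **That section 3 contradicts section 2.3.3.** A stated minimum and a later caution are in tension, no more. Nor do the documents show that a null result will be misread, since they warn of that risk themselves.

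What the reply does not rescue is the sentence's role. It is the only basis offered for the comparison, in a trial that enrols exactly the number it names. The f = 0.25 route does not help either, because it needs an effect that the article's own scale calls large. The pilot label could support a different rationale, but section 2.3.3 does not give one.

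**Conclusion.** The point holds in a bounded form: section 2.3.3 does not justify 60 for this trial. The survey-precision sentence is correct arithmetic for a question the trial does not ask. The medium-effect sentence cannot be reproduced from what is stated. On its ordinary reading the size falls well short, at about half of the 128 needed for 80% power. The conclusion about the first sentence needs no assumption. The power figures rest on two-sided 5% testing, 30 analysed per group and d on the outcome SD, and for the planned test also on the assumed correlation. Because section 2.8 excludes missing data and no dropout allowance is stated, they are upper figures for an enrolment of 60.

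**What to change.** In section 2.3.3:

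- Delete the survey-precision sentence as a basis for the group comparison.
- Replace the medium-effect sentence with what 30 per group delivers for the planned interaction at two-sided 5%. If r = 0.5, that is 80% power at d of about 0.74, 48% power at d = 0.5, and a 95% confidence interval half-width of about 0.52 SD. Show the range over plausible correlations beside it, and mark the correlation as an assumption.
- Justify 60 on pilot and availability grounds, in line with section 3. The article mentions a population of 70 and limited devices but does not derive 60 from the devices, so the sponsor should give the actual reason.

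Baseline-adjusted figures belong there only if the plan adopts a baseline-adjusted group comparison. At present section 2.8 uses baseline covariates only in the mediation models. Softening the aim in section 4 from demonstrating to estimating the effect is optional wording.

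The cost is a rewritten paragraph. There are no extra students and no design change, but the stated capability becomes less favourable.
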